### Randomization

Patients are randomized 1:1 to an intervention (INT) group (*n* = 150), receiving a theoretical and practical exercise counseling on top of standard care, and a control (CON) group (*n* = 150), receiving only standard care including general physician recommendations for daily PA.

Randomization is stratified by center and, within each center, by age and type of diabetes treatment (non-insulin versus insulin therapy), using a permuted-block randomization software that randomly varies the block size. To ensure allocation concealment, randomization is centralized at the Center for Outcomes Research and Clinical Epidemiology (CORE). After randomization, participants, physicians and exercise specialists are unblinded to group assignment, as blinding is not feasible in exercise-intervention studies.

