### Statistical analysis

Sample size calculation is based on preliminary accelerometer data showing that daily PA in sedentary, physically inactive T2DM patients is 24.2 ± 9.4 METs ∙ h^−1^ ∙ wk^−1^. To observe a 15 % increase in daily PA with a statistical power of 90 % (α = 0.05) by unpaired t-test, 142 patients per arm are needed (284 total). A sample size of 300 patients will allow supporting a 5 % dropout rate, as detected in the EXE group from the IDES [14].

The χ^2^ test for categorical variables and the Student’s t test or the corresponding nonparametric Mann–Whitney test for continuous variables will be utilized to compare patients’ characteristics at baseline.

The intent-to-treat analysis for primary and secondary endpoints will be applied to all randomized patients with a baseline and at least one post-baseline value. The efficacy of the intervention, as compared with standard care, on the primary and secondary endpoints will be assessed by a repeated measures analysis of covariance (ANCOVA - using PROC MIXED in SAS software) of change from baseline to the end-of-study. In case of differences between groups in baseline values, we will consider a baseline adjustment to improve power. The differences between end-of-study and baseline QoL scores and summary measures between the two groups will be compared using the Mann–Whitney U-test, while changes in QoL parameters within each group (end-of-study versus baseline) will be tested using the Wilcoxon test.

To account for change in medication throughout the study period, which might affect performance with respect to cardiovascular risk factors, we will perform both multiple regression and sensitivity analyses. In the regression models, the dependent variable will be represented by baseline to end-of-study changes. Treatment at baseline and treatment initiation during the study will be included in the model as dichotomous variables (yes versus no), whereas drug dosage will be not taken into consideration. Sensitivity analysis will be conducted by comparing study arms after exclusion of the patients who modified the treatment.

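### Baseline adjustment of the primary model is only to be considered, and only if the groups differ at baseline; it should be fixed in advance, because its gain does not depend on imbalance

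*Protocol article*

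**What the plan says.** All statements are in the protocol article, under Statistical analysis unless noted.

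- The effect on primary and secondary endpoints is assessed by a "repeated measures analysis of covariance (ANCOVA - using PROC MIXED in SAS software) of change from baseline to the end-of-study". No covariate is listed.
- The next sentence reads: "In case of differences between groups in baseline values, we will consider a baseline adjustment to improve power". No threshold for a difference is given, and even when one is found the adjustment is only considered.
- Chi-square, t or Mann–Whitney tests "will be utilized to compare patients’ characteristics at baseline". The text does not connect these tests to the adjustment decision.
- The sample size rests on an unpaired t-test. Preliminary data show that "daily PA in sedentary, physically inactive T2DM patients is 24.2 ± 9.4", and the aim is "To observe a 15 % increase in daily PA" with 90% power and α = 0.05, giving 142 per arm.
- A full statistical analysis plan is promised before unmasking. Nothing in that promise withdraws the conditional rule, and no other section makes baseline an unconditional covariate.
- Two accelerometer periods could be taken as baseline. Under Recruitment, patients wear the device for one week between R2 and R3, before allocation. Under Assessment of PA, the 4-month wear is described as the baseline one, but that wear starts at R4, when patients learn their group and receive counseling or advice.

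**The concern.** The rule ties adjustment to the wrong condition. A baseline covariate removes outcome variance that baseline predicts, and it does so in a perfectly balanced trial too. Waiting for an imbalance withholds the adjustment in most trials where it would help.

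The rule also leaves open what counts as a difference and what follows from one. Two analysts with the same data could report different primary estimates, standard errors and possibly different conclusions, each in keeping with the text. The article wants a prespecified analysis to guard against selective reporting, and this sentence works against that aim.

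If no adjustment is made, the fallback is an unadjusted change score. It is less precise than the adjusted analysis, and part of any chance baseline difference stays in the estimate.

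**Working it through.** **Inputs.** From the article: mean 24.2, SD 9.4, a 15% increase, 90% power, α = 0.05, 142 per arm. Assumed, because the article does not give them: the baseline to end-of-study correlation r, the same SD at both times, and a two-sided test. The check uses a single end-of-study value, not the full repeated measures model.

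**The plan's own figure.** Difference = 0.15 × 24.2 = 3.63, and 3.63 / 9.4 = 0.386 SD. A two-sided normal approximation gives 141 per arm; the noncentral t gives 141.9, so 142. The stated figure reproduces.

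**Power at 142 per arm.**
- SD of the unadjusted change = 9.4 × √(2(1 − r))
- Residual SD under ANCOVA = 9.4 × √(1 − r²)
- Variance ratio, ANCOVA to change = (1 + r)/2, below 1 for every r below 1
- Power ≈ Φ(3.63 / (SD × √(2/142)) − 1.96)

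| r | SD change | SD ANCOVA | Power change | Power ANCOVA | n per arm for 90%, change / ANCOVA |
|---|---|---|---|---|---|
| 0.3 | 11.12 | 8.97 | 78.5% | 92.7% | 198 / 129 |
| 0.5 | 9.40 | 8.14 | 90.2% | 96.4% | 141 / 106 |
| 0.7 | 7.28 | 6.71 | 98.7% | 99.5% | 85 / 72 |

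At r = 0.5 the change score has the same SD as a single measurement, so it just meets the planned 90%. Below 0.5 it does not.

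**Imbalance left in the estimate.** The standard error of the baseline difference is 9.4 × √(2/142) = 1.116, so a difference at the edge of p = 0.05 is 1.96 × 1.116 = 2.19 MET-h/wk. The change score carries (1 − r) of it, with opposite sign:
- r = 0.3: 0.7 × 2.19 = 1.53, or 42% of 3.63
- r = 0.5: 0.5 × 2.19 = 1.09, or 30%
- r = 0.7: 0.3 × 2.19 = 0.66, or 18%

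**Type I error given an imbalance.** With a baseline difference of 1.9 standard errors, the change-score statistic under the null has mean shift 1.9 × √((1 − r)/2) and SD √((1 + r)/2). At r = 0.3 these are 1.124 and 0.806, giving about 15% rejection. At r = 0.7 they are 0.736 and 0.922, giving about 9%.

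**One possible version of the rule.** The article sets no trigger. As an illustration only, adjusting when a baseline t-test has p < 0.05 was simulated (30,000 trials per setting). Adjustment occurred in about 5% of trials.

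| r | Power, conditional rule | Power, always ANCOVA | Overall type I error, conditional rule |
|---|---|---|---|
| 0.3 | 79.7% | 92.5% | 4.1% |
| 0.5 | 91.2% | 96.2% | 4.4% |
| 0.7 | 98.8% | 99.5% | 4.6% |

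**The case against.** **The model is called an analysis of covariance, so a covariate is implied.** This is fair as far as it goes. But the next sentence makes baseline adjustment conditional, so either baseline is out by default or the two sentences conflict. Both need correcting.

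**The promised analysis plan may settle it.** It may. The rule is nevertheless stated in the article, not left out of it, and an analysis plan faithful to the article would inherit it.

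**The loss may be small.** This stands in part. At r = 0.7 the power gap is under one percentage point, and at r = 0.5 the unadjusted analysis still reaches 90%. If the follow-up SD exceeds the baseline SD, which is plausible because patients are selected for inactivity, the regression slope exceeds r and the carried-over imbalance shrinks. The planned model also uses several visits, so the figures are indicative. An imbalance close to 1.9 standard errors is itself uncommon.

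**Stronger readings that the documents do not support.**
- A reader might infer that the planned baseline significance tests decide the adjustment. The article does not say so; a p < 0.05 trigger is an assumption.
- A reader might infer that choosing the model this way inflates type I error. For the fixed rule simulated above it does not, and the change score is unbiased over randomizations. Open discretion could still permit choosing between two results, but the article gives no rule from which that could be quantified.
- A reader might count the absence of the stratification factors from the model as an error. A condensed article may leave the covariate list to the analysis plan.
- A reader might take the rank test for quality of life ("The differences between end-of-study and baseline QoL scores and summary measures between the two groups will be compared using the Mann–Whitney U-test") as a contradiction of the general model. It reads as a stated exception for a secondary endpoint and is a separate matter.

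**Conclusion.** The point holds for the conditional adjustment sentence. Its rationale is wrong, and it leaves the primary model to be chosen after the baseline data are known. The consequences are lost precision, bias conditional on the realised imbalance, and analyst discretion.

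The size depends on a correlation that the article does not report. The power cost is about 14 percentage points at 0.3, 6 at 0.5 and less than 1 at 0.7, and the stated 90% is missed only below 0.5. These figures assume equal SDs and a single end-of-study value. That adjustment should not wait for an observed imbalance does not depend on them.

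**What to change.** Replace the conditional sentence with: *The primary and secondary continuous endpoint models include the pre-randomization value of that endpoint as a covariate, regardless of observed balance.* State that baseline comparisons play no part in deciding on adjustment.

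For physical activity and sedentary time, name the one-week R2–R3 accelerometer reading as the baseline value. The 4-month wear starting at R4 must not be used: it follows allocation, so adjusting for it would condition on data that the intervention may already have changed.

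Adding center, age and insulin use as covariates is sensible because randomization is stratified by them, but it is optional here.

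The cost is wording. The baseline values are already collected, and no more patients are needed: under the assumptions above, ANCOVA needs 129 per arm at a correlation of 0.3 and fewer at higher values, against the 142 planned.

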The joint position statement of the American College of Sports Medicine (ACSM) and the American Diabetes Association (ADA) [10] recommends that individuals with T2DM perform at least 150 minutes/week of moderate-to-vigorous aerobic exercise, plus moderate-to-vigorous resistance training at least 2–3 days/week. In addition, the ACSM/ADA guidelines recommend that individuals train under the supervision of qualified exercise trainers, particularly when undertaking resistance exercise, to ensure optimal health benefits and to minimize injuries; individuals are also encouraged to increase total daily unstructured (commuting, occupational, home, and leisure time [LT]) PA. These recommendations are based on a large body of experimental evidence which has been accumulating during the last decade. Two randomized controlled trials (RCTs), the Diabetes Aerobic and Resistance Exercise (DARE) study [11] and the Health benefits of Aerobic and Resistance Training in individuals with type 2 Diabetes (HART-D) study [12], have demonstrated that combined aerobic and resistance training is more effective than either one alone in reducing hemoglobin (Hb) A_1c_ in patients with type 2 diabetes. A systematic review and meta-analysis including the DARE and HART-D studies showed that structured exercise training, either aerobic, resistance, or both, is associated with HbA_1c_ reduction in patients with type 2 diabetes, especially if more than 150 minutes/week is undertaken and when combined with dietary advice [13]. Furthermore, another RCT, the Italian Diabetes and Exercise Study (IDES), showed that a strategy combining a supervised mixed (aerobic and resistance) exercise training program with structured exercise counseling was more effective than counseling alone in improving physical fitness and quality of life (QoL), ameliorating HbA_1c_ and other modifiable cardiovascular risk factors, reducing coronary heart disease (CHD) 10-year risk scores, and decreasing the number and/or dosage of medications, in a large cohort of sedentary subjects with T2DM [14–16]. Finally, recent findings suggest that higher sedentary time (SED-time) in T2DM individuals is associated with higher metabolic risk, independently of measured confounders and time spent in moderate-to-vigorous PA (MVPA) [17, 18], thus supporting the hypothesis that the biological responses to SED-time likely influence metabolic risk through pathways distinct from those of MVPA [19, 20].

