With regard to possible risks of bias, we anticipate that, according to the Cochrane Collaboration [75], the risk of selection bias is low, due to the use of adequate methods for sequence generation and allocation sequence concealment, although patients who agree to participate in a lifestyle intervention program might be different from those who refuse. Moreover, though blinding of participants and investigators is impossible in exercise intervention studies, the risks of performance, detection, and attrition bias are also limited for several reasons. Regarding performance, despite the fact that independently of intervention, participants might be influenced by knowledge of group assignment in adopting and maintaining a physically active lifestyle, the possibility that unblinding to group assignment may result in an overestimation or an underestimation of intervention effects is low. On the one hand, subjects from the control group of the IDES performed a considerable amount of PA [14] and, though PA measurements are known to affect physical activity behavior [76], this would impact on PA volume of both groups. On the other hand, investigators are asked not to provide subjects from the control group with PA advice other than general recommendations for increasing the amount of daily PA (and decreasing the SED-time), and intensification of pharmacological treatment to compensate for lower PA in these individuals will be accounted for in the statistical analysis. Regarding detection, because the primary outcome and some secondary outcomes (physical fitness and cardiovascular risk factors) are objective, the risk of bias is low on both the participant’s and investigator’s side, although study subjects might be influenced by knowledge of group assignment when filling in questionnaires for musculoskeletal disturbances, well-being/depression, and health-related QoL. Regarding attrition, in the IDES, knowledge of group assignment did not affect remaining in the trial for the entire study period as participants from the control group dropped out at a rate and for reasons similar to those of the exercise group [14]. Moreover, as reported above, the risk of attrition bias due to missing data has been adequately prevented and will be treated according to a recent National Research Council report on the topic [57].

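### The planned medication analyses of the cardiovascular risk factors adjust for, or exclude on, drug changes made after randomization, so they cannot by themselves account for drug intensification

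*Protocol article*

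**What the plan says.** The main efficacy analysis for primary and secondary endpoints is a repeated-measures ANCOVA in every randomized patient who has a baseline measurement and one or more later ones (Statistical analysis). It does not condition on medication.

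Two further analyses address medication changes that might affect the cardiovascular risk factors:

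- A regression of the change from baseline to end of study: "Treatment at baseline and treatment initiation during the study will be included in the model as dichotomous variables (yes versus no"). Dose is left out.
- An exclusion analysis: "Sensitivity analysis will be conducted by comparing study arms after exclusion of the patients who modified the treatment".

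The Discussion, in its paragraph on risks of bias, refers to the control group and says that "intensification of pharmacological treatment to compensate for lower PA in these individuals will be accounted for in the statistical analysis". This is one of its reasons for calling performance bias limited.

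The Background reports that the intervention in the predecessor trial was more effective than counseling alone in "decreasing the number and/or dosage of medications".

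**The concern.** A drug started or changed during follow-up is not a baseline characteristic. If it depends on how the patient is doing, and the intervention affects how the patient is doing, then adjusting for it or selecting on it compares groups that randomization did not create.

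The exclusion removes patients whose treatment was intensified because control was poor. As worded, it also removes patients whose drugs were reduced because they improved. The yes/no initiation term registers neither dose changes nor reductions, although reduction is an effect the Background credits to the earlier intervention.

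What is at stake is interpretation. If the two analyses are read as robustness checks, a smaller effect could be taken to mean no metabolic benefit beyond drugs. Agreement with the main result could be taken as proof that intensification did not matter. Neither inference would be sound.

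**Working it through.** **The premises, from the article**

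1. Drug change comes after allocation. Table 2 places the initial prescription at R3, allocation at R4 and prescription adjustment at all nine follow-up visits. Baseline treatment is thus a legitimate covariate; initiation and modification during follow-up are not.
2. Drug change responds to the endpoints. Under Follow-up, clinical and laboratory results are discussed and prescriptions adjusted. Under Standard care, all patients are treated toward glycemic, lipid, blood-pressure and weight targets. These measures are also secondary outcomes, taken every 4 months.
3. Drug change may differ by arm. Physicians know the allocation (Randomization), and the Discussion contemplates compensating intensification in controls.

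**The plan's only size figure**

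The sample size uses "daily PA in sedentary, physically inactive T2DM patients is 24.2 ± 9.4 METs" (per hour per week, as the article writes the unit) and a 15 % increase: 0.15 × 24.2 = 3.63, and 3.63/9.4 = 0.386 SD. With two-sided α = 0.05 and 90 % power, the normal approximation gives 141 per arm and the exact t calculation 142, as stated. Allowing for 5 % dropout, 284/0.95 = 298.9, so 299 against 300 planned. This reproduces and is not at issue. It concerns physical activity; the article states no planned effect for HbA1c, lipids or blood pressure.

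**Illustrative simulation (all inputs assumed; 400,000 patients per scenario)**

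Baseline b has SD 1, unmeasured progression u has SD 0.7, arm a is 0 or 1, and e is noise with SD 0.4, drawn separately each time.

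- Interim value = b + u + θa + e.
- logit P(drug started) = −0.5 + slope × interim value.
- Final value = b + u + θa + e + drug effect × (drug started).
- Outcome = final value − b.

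| Direct effect θ | Drug effect | Slope | All patients | Regression on initiation | Same, plus baseline value | Exclusion | Started drug, CON / INT |
|---|---|---|---|---|---|---|---|
| 0 | 0 | 3 | 0.002 | 0.002 | 0.003 | −0.001 | 45.4 % / 45.4 % |
| −0.5 | 0 | 0 | −0.497 | −0.497 | −0.497 | −0.492 | 37.8 % / 37.8 % |
| −0.5 | 0 | 1 | −0.497 | −0.464 | −0.459 | −0.466 | 40.6 % / 31.9 % |
| −0.5 | 0 | 3 | −0.497 | −0.420 | −0.387 | −0.427 | 45.5 % / 31.8 % |
| −0.5 | −0.6 | 1 | −0.452 | −0.471 | −0.466 | −0.474 | 40.6 % / 31.8 % |
| −0.5 | −0.6 | 3 | −0.420 | −0.425 | −0.392 | −0.432 | 45.3 % / 31.7 % |
| −0.3 | 0 | 1 | −0.302 | −0.282 | −0.279 | −0.286 | 40.6 % / 35.2 % |
| −0.3 | −0.6 | 3 | −0.246 | −0.250 | −0.229 | −0.251 | 45.3 % / 36.9 % |

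Attenuation against the direct effect, slopes 1 to 3:

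- θ = −0.5: from 1 − 0.474/0.5 = 5.2 % to 1 − 0.387/0.5 = 22.6 %.
- θ = −0.3: from 1 − 0.286/0.3 = 4.7 % to 1 − 0.229/0.3 = 23.7 %.

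Scenarios with no effect scatter by up to 0.007 around zero, so these limits are approximate.

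With slope 0 there is no bias. With no intervention effect and one prescribing rule for both arms there is none either. In the sixth row, the exclusion keeps 1 − 0.453 = 54.7 % of CON and 1 − 0.317 = 68.3 % of INT.

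That row also shows why agreement is not reassurance. All patients (−0.420), regression (−0.425) and exclusion (−0.432) nearly coincide, yet the effect without drugs is −0.5.

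**If prescribing thresholds differ by arm**

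Suppose there is no true effect, and patients above an arm-specific threshold on a trigger correlated r with the outcome are excluded. The mean of those remaining shifts by −r·φ(z)/(1 − p), where p is the share excluded and z the cut-point.

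- 30 % of CON and 15 % of INT excluded: the difference is 0.222r, or 0.07 to 0.18 SD for r = 0.3 to 0.8, in favour of CON.
- 40 % and 20 % excluded: 0.294r, or 0.09 to 0.24 SD.

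This formula ignores the drug's own effect on the final value.

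**The case against.** The strongest reply is that these are supplementary analyses of secondary endpoints, one of them expressly a sensitivity analysis, and that the main analysis already includes everyone regardless of drug changes. That stands. A reader might infer that the plan's main risk-factor comparisons, or even the primary result, are biased. The article does not support this: the ANCOVA does not condition on medication, and the two analyses are confined to cardiovascular risk factors.

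A reader might also take the 0.07 to 0.24 SD shifts as the expected bias and set them against 0.386. That does not hold either. Unequal exclusion with no true effect requires prescribing thresholds that differ by arm. Open-label care makes this possible, but the article does not state it. The 0.386 belongs to physical activity, so it is no yardstick for risk factors. The Discussion gives no rate of intensification in controls.

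Finally, the all-patients comparison answers a different question. When the drug works, it includes the drug's compensating effect, and in some scenarios the planned analyses lie closer to the effect without drugs (−0.474 by exclusion against −0.452 for all patients, where the direct effect is −0.5). With no drug effect, the all-patients result is closer. This argues against insisting on deletion. It does not make the two analyses valid safeguards.

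**Conclusion.** The point holds for the two medication analyses and for the Discussion's reliance on them, and no further. They condition on events that follow randomization, respond to the endpoints and may differ by arm. They are therefore not randomized comparisons and cannot alone account for intensification.

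Attenuation of roughly 5 to 24 % is an illustration. It rests on an assumed prescribing model, assumed drug effects and about 41 to 46 % of controls starting a drug, and it does not model dose changes or reductions. Neither the size nor the direction in this trial can be derived from the article. This should be fixed; it does not threaten the primary conclusions.

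**What to change.** In the analysis plan still to be written before unmasking:

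- State that conclusions on risk factors rest on the all-randomized comparison regardless of drug changes.
- Add a between-arm comparison of drug initiation, intensification and reduction as an outcome, as far as these are recorded. The article does not say whether dose and reductions are captured.
- Label the initiation-adjusted regression and the exclusion analysis as exploratory, non-randomized comparisons and not as robustness checks. Keep baseline treatment as a covariate.
- If an effect without drug intensification is wanted, define it explicitly and estimate it under stated assumptions, with a sensitivity check on them.
- Amend the Discussion so that it no longer presents these analyses as accounting for intensification.

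The cost is wording, some extra analysis work and a less reassuring statement on performance bias. Any estimate of the effect without intensification will rest on assumptions that the data cannot fully test.

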In order to treat attrition, we will assume that data are missing at random, use adjustment methods for missing data, and conduct a sensitivity analysis to assess the robustness of inferences about treatment effects to various missing-data assumptions [57]. In particular, repeated measures models with an autoregressive correlation type matrix will be applied in order to account for both missingness at random and potential correlation within subjects. These methods are more efficient in that they allow evaluating all subjects, even those with incomplete data [58, 59]. Moreover, to guarantee replicability and avoid outcome selective reporting, a fully specified statistical analysis plan will be written before unmasking.

Statistical analyses will be performed by at the CORE using SAS software release 9.3 (Cary, NC, USA).

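### An autoregressive matrix for changes from a shared baseline does not secure validity under missing at random, and the rank tests for quality of life drop patients whom the plan says it will evaluate

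*Protocol article*

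**What the plan says.** All of this is in the Statistical analysis section of the protocol article.

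- **Model.** Primary and secondary endpoints are analysed by a repeated measures ANCOVA (PROC MIXED) of change from baseline. Baseline adjustment is only to be considered, and only if the groups differ at baseline.
- **Covariance.** "repeated measures models with an autoregressive correlation type matrix will be applied in order to account for both missingness at random", and also for correlation within subjects. The stated advantage is that "they allow evaluating all subjects, even those with incomplete data".
- **Missing data.** "we will assume that data are missing at random, use adjustment methods for missing data". The plan also promises to vary these assumptions in a sensitivity analysis. The content of both is left open.
- **Analysis set.** The intent-to-treat analysis "will be applied to all randomized patients with a baseline and at least one post-baseline value".
- **Quality of life (QoL).** Between arms the named test is Mann-Whitney, and within each arm it is Wilcoxon. The between-arm sentence opens: "The differences between end-of-study and baseline QoL scores and summary measures between the two groups will be compared using".
- **Later detail.** "a fully specified statistical analysis plan will be written before unmasking".

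Elsewhere in the article, Outcome measures lists QoL as a secondary outcome. Table 2 schedules the SF-36 at F1, F3, F4, F6, F7 and F9. Table 2 and Assessment of PA give accelerometer wear of 4 months for the period that ends at F1, and 7 days at each later visit.

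**The concern.** The plan credits the autoregressive matrix with handling missingness at random. A correlation structure does not do that. Under MAR, a likelihood analysis is valid if the mean and covariance models are adequate, because the covariance determines how observed visits inform the missing ones.

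Here the response makes an autoregressive structure doubtful. Every change subtracts the same baseline, which puts a common component into all nine visits. Variances may also grow with time, and the wear period differs between F1 and later visits. A matrix that is wrong in these ways can give standard errors that are too small even with no missing data. With dropout that depends on earlier outcomes, it can leave part of the selection bias in the month-36 comparison.

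The QoL tests are a second, separate fault. A test on end-of-study minus baseline needs a month-36 score, so unless scores are imputed it falls outside the approach that the same section adopts for incomplete data.

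**Working it through.** **1. The plan's own figure.** Target difference: 0.15 × 24.2 = 3.63, SD 9.4. Two-sided normal formula: n = 2(1.96 + 1.2816)² × 9.4² / 3.63² = 140.9, so 141 per arm. The exact t calculation gives 142 (power 0.900), as stated. 284/0.95 = 299, against 300 planned. The sample size reproduces and this point does not affect it.

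**2. Covariance of changes.** For raw values with variance σ² and correlations r, with baseline as visit 0:

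Cov(Yj − Y0, Yk − Y0) = σ²(1 + r_jk − r_j0 − r_k0).

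*Exchangeable raw values (correlation ρ):* every change has variance 2σ²(1−ρ) and every pair has covariance σ²(1−ρ). The correlation is therefore 0.5 at every lag. The best-fitting AR(1) has parameter 0.5 and implies 0.5⁸ = 0.004 between F1 and F9.
- Visit average: true relative variance (1 + 8 × 0.5)/9 = 0.556. AR(1) gives [9 + 2Σ(9−k)0.5^k]/81 = (9 + 14.008)/81 = 0.284. SE ratio √(0.284/0.556) = 0.715. Type I error 2Φ(−1.96 × 0.715) = 16.1%.
- Month 36: the variance is right, so type I error is 5.0%.

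*Raw values exactly AR(1) at 0.8:* the changes have variance 2(1−0.8)σ² = 0.40σ² at F1 and 2(1−0.8⁹)σ² = 1.73σ² at F9. A constant-variance AR(1) fitted by expected likelihood (minimising log|V| + tr(V⁻¹S)) settles at 1.18σ². SE ratio at month 36: √(1.18/1.73) ≈ 0.82. Type I error 10.6%.

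The same method, and a simulation with 150 per arm, complete data and 3,000 replicates for the rows marked †, give:

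| Assumed raw-value structure | AR(1), month 36 | AR(1), visit average |
|---|---|---|
| Exchangeable | 5.0% | 16.1% |
| AR 0.6 | 7.7% | 8.0% |
| AR 0.8 | 10.6% | 6.2% |
| Shared 0.6, AR 0.2 (lag-one 0.7), noise 0.2 † | 6.1% | 11.7% |
| Shared 0.3, AR 0.5 (lag-one 0.8), noise 0.2 † | 8.7% | 10.4% |
| AR 0.8, baseline-adjusted † | 8.3% | 6.1% |

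An unstructured matrix gave 4.5-5.6% in all simulated cases. The last row shows that baseline adjustment alone does not remove the problem.

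**3. Bias at month 36.** Assumptions: SD 9.4, nine visits, 60,000 per arm, monotone dropout driven by the last observed change (hence MAR), and true effect 0 or 3.63. Structures: the two mixtures above and AR 0.8. Absolute bias in MET-h/week:

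| Dropout | AR(1) | Completers only |
|---|---|---|
| Same mechanism in both arms, about 4-7% | at most 0.12 | at most 0.24 |
| Same mechanism in both arms, about 18-28% | at most 0.26 | at most 0.62 |
| Outcome-dependent in one arm, about 4% against 7-18% | 0.22-0.78 | 0.41-2.34 |
| Outcome-dependent in one arm, about 19-20% against 23-41% | 0.89-2.04 | 1.43-4.78 |

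The unstructured matrix stayed within ±0.14 throughout, so differences of that size are simulation noise. Against 3.63, the third row is 0.22/3.63 = 6% to 0.78/3.63 = 21%.

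**4. QoL.** Three statements in one section do not fit together: secondary endpoints go to the mixed model, QoL (a secondary endpoint) goes to a rank test of end-of-study change, and subjects with incomplete data are evaluated. Without imputation, a patient with SF-36 scores at baseline, F1, F3, F4, F6 and F7 but none at F9 is in the analysis set yet contributes nothing to the QoL test. The completer column in step 3 shows the direction of the risk, on the PA scale only.

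**5. Analysis set.** At 5% dropout, at most 0.05 × 300 = 15 patients could lack any follow-up. 285 remain, which is still at least 142 per arm if losses are balanced. In a model of change, such patients carry no likelihood information. MAR validity suffers only if their absence depends on something outside the model, such as baseline when it is not a covariate.

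**The case against.** - **The article does not say AR(1).** It names only an autoregressive type. Heterogeneous variances or an added random intercept are possible in PROC MIXED, and the promised analysis plan may specify them. This stands as a limit on the figures. Heterogeneous variances would answer the unequal-variance part, but not the shared-baseline correlation. The article also presents the structure as the means of handling MAR, which is a stated choice rather than an omitted detail.
- **A sensitivity analysis and adjustment methods for missing data are promised.** They count in the plan's favour and could cover some of the bias. They do not repair a misspecified primary covariance, since the type I error above arises with complete data.
- **A reader might infer a 16% false-positive rate for the primary test.** The documents do not support that. The 16% belongs to a visit average under exchangeable raw values, and month 36 in that scenario is at 5.0%. The wording of change to end-of-study points to month 36.
- **A reader might infer that about a fifth of the target effect could be artefact.** That takes about 15% outcome-dependent dropout in one arm: 0.75 MET-h/week, or 0.75/3.63 = 21%, if raw values are exchangeable at 0.5. The plan expects 5% dropout, and the Discussion reports similar rates and reasons in both arms of the earlier IDES trial. The same set-up with 5% dropout in one arm gives 0.24, about 7%.
- **The phrase about evaluating all subjects can be read as keeping partial follow-up.** That is fair, and it makes the analysis-set issue mainly one of labelling.
- **Completer-only use of QoL is an inference.** It is, but it follows from the named test unless imputation is added.

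**Conclusion.** The point holds in a limited form. The autoregressive matrix is a poorly justified choice for changes from a shared baseline, and it does not itself account for MAR. Read as homogeneous AR(1), complete-data type I error runs from about 5% to 11% at month 36 and from about 6% to 16% for a visit average. At the planned dropout with a common mechanism, bias is negligible. With outcome-dependent dropout in one arm it is roughly 0.2-0.8 MET-h/week at low dropout and more at higher dropout. An open-label, 36-month behavioural trial cannot rule that out. All these sizes rest on assumed correlations and dropout models, because the article gives no within-patient correlations and no dropout by arm.

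The QoL contradiction needs no numerical assumption. It concerns one secondary outcome, and the passages should be reconciled. The analysis-set wording is a lesser, mainly labelling, fault. None of this shows that the MAR strategy as a whole fails or that the sample size is wrong.

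**What to change.** In the analysis plan, before unmasking:

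1. Specify an unstructured covariance for the mixed model, with a named fallback structure and robust variance if it does not converge.
2. Include baseline in the model always, not conditionally on an observed difference.
3. State the arm difference at month 36 as the primary contrast.
4. Analyse SF-36 scores with the same model, using all scheduled visits, and keep the rank test as a sensitivity analysis.
5. Either include all randomised patients or stop calling the set intent-to-treat.
6. Replace the statement that the autoregressive matrix accounts for MAR with one that attributes validity to the likelihood model.

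The cost is wording and a covariance option in PROC MIXED. The matrix needs 9 × 10/2 = 45 parameters for nine visits, or 10 × 11/2 = 55 if baseline is part of the response. That is affordable with 300 patients, and no data collection changes.
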